#### VO_2_-Max Test Procedure

At the end of the A1 phase, subjects will perform a VO_2_-Max test to determine individual training load, as described by Mavromatti et al. (28). In brief, the exercise test will be conducted on an electronically braked cycle ergometer (Excalibur Sport, Lode, the Netherlands), integrated with a cardiopulmonary-monitoring system that controls the work rate protocol on the ergometer and records breath-by-breath measurements of VO_2_, VCO_2_, ventilation, and heart rate (Cosmed Benelux BV, the Netherlands) throughout the test. Handlebars and saddle of the cycle ergometer will be adjusted to match each participant's anthropometrics. The work rate protocol consists of 2-min steps starting with unloaded cycling and then increasing to 50 W, and thereafter increasing in steps of 25 W. While the ergometer maintains a constant workload, independent of cadence, participants are instructed to aim for cadence of ~60–80 rpm. At the end of each step, participants are asked to rate their level of exertion (rating of perceive exertion) using the Borg RPE 10-point category ratio scale (Borg CR10 scale, “0” to “10”) (29). Participants are verbally encouraged to carry on for as long as possible. The exercise test is terminated by voluntary exhaustion, by a cadence <45 rpm or for safety reasons, compliant with the American College of Sports Medicine's guidelines for clinical exercise testing (30). Subjects are asked to abstain from exercise and consumption of alcohol or caffeine 12 h prior to testing.

#### Outcome Measures

Outcome measures are chosen based on recommendations by the Movement Disorders Society (31), the 2014 European guideline of physical therapy for PD (32), and recommendations by the members of the project team, including several PD patients. Table 1 shows the timeline and assessment schedule for demographics and all outcome parameters. Demographics include age, sex, disease duration, Hoehn–Yahr stage, medication schedule and dosage, and MoCA score.

The primary study parameter is disease severity measured every 4 weeks during baseline A1 and A2 and intervention and two times during baseline A3 with the MDS-UPDRS part III (motor examination) during on-state (33).

Secondary outcome parameters were pre–post intervention outcome measures will be administered before and after each study phase; and disease status with MDS-UPDRS 1, II, and IV (33). Cognition will be evaluated with the MoCA (34), the Stroop test (35), and the Trail Making Test for executive function [TMT; Olchik et al. (36)] and the PD Cognitive Functioning Rating Scale (PD-CFRS) (37). Activities of daily living and quality of life were assessed with self-report questionnaires: the Nottingham Extended ADL index (NEAI) (38) and the Parkinson Disease Questionnaire (PDQ-8) (39). Mood and sleep will be assessed using the Beck Depression Inventory questionnaire (31) and the Scopa Sleep scale (40), respectively.

Weekly outcomes are motor performance, namely, the 10-meter walk test (41), the Timed “Up-and-Go” test (TUG) (42), and the one-leg stance test (43). In addition, daily physical activity with a wrist-worn activity tracker will be recorded throughout the study. For weekly self-report outcomes, we will use Ecological Momentary Assessment methodology (44), asking frequent (weekly in baseline phases, three times a week in intervention phases), short online survey questions about non-motor functions using Castor EDC (45): Mood will be assessed with a visual analog scale (VAS) score rating: “Can you rate your current mood on a scale from “1” to “10”?” (a score of “1” represents “very sad”; a score of “10” represents “very happy”). Sleep performance will be assessed with a VAS score rating: “Can you rate how well you slept last night on a scale from “1” to “10”?” (A score of “1” represents “very bad”; a score of “10” represents “very good”). Cognitive function will be assessed with a VAS score for “ability to concentrate”: “Can you rate well you are able to concentrate on daily tasks on a scale from “1” to “10”?” (a score of “1” represents “very bad”; a score of “10” represents “very good”). In addition, we will ask the subjects to keep a logbook of their attended sessions and perceived effort (RPE).

Blood samples (for serum BDNF, NfL, and α-synuclein) will be collected by a trained nurse once a week in the baseline and training phases (A1 and B/C). Blood draw frequency is decreased to once every 2 weeks in the washout phases (A2 and A3) to reduce patient burden. Twenty-milliliter blood samples will be taken from the antecubital vein at rest in the morning hours between 08:00 and 10:00 in the fasting state. We will use anticoagulant-free tubes, which be placed on ice (−80°C) until further analysis. BDNF concentration will be measured with a commercially available and in-house validated kit (Quanterix Simoa). Serum NfL and α-synuclein concentrations will be measured using an in-house developed Homebrew Simoa assay (17, 46).

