## Methods

### Study Design

We will use a single-subject alternating treatment approach with A1-B-A2-C-A3 or A1-C-A2-B-A3 design to study the effects of HIIT on motor and non-motor performance and neuroplasticity and neurodegeneration biomarkers such that subjects will perform both the HIIT (B-phase) and the moderate CAE training (C-phase) for 4 weeks. After a baseline (A1) period of 4 weeks, the first intervention period of 4 weeks will take place (B or C), followed by a washout period of 8 weeks without an intervention (A2), the second intervention period of 4 weeks (B or C), and finally a third washout period of 8 weeks (A3). Each patient therefore experiences the full set of treatment approaches. The order of interventions B and C will be randomized for each participant (i.e., ABACA or ACABA, two of each, four participants total) using a random sequence generator. Assessment will be done by Good Clinical Practice (GCP)-trained blinded assessors.

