**Table d38e2389:** 

	**Phase**	**Baseline A3**																																			
	**Week**	**1**			**2**			**3**			**4**			**5**			**6**			**7**			**8**		
	**Session**	**s1**	**s2**	**s3**	**s1**	**s2**	**s3**	**s1**	**s2**	**s3**	**s1**	**s2**	**s3**	**s1**	**s2**	**s3**	**s1**	**s2**	**s3**	**s1**	**s2**	**s3**	**s1**	**s2**	**s3**
Tests	Cardiac Screening																								
	Demographics																								
	VO_2_ test																								
Motor	UPDRSI-IV	x																							x
	TUG	x						x						x						x					x
	10m walk	x						x						x						x					x
	one-leg-stance	x						x						x						x					x
Cognition	MoCa																								x
	Stroop test	x																							x
	TMT	x																							x
	PD-CFRS	x																							x
	VAS-concentration	x			x			x			x			x			x			x					x
Mood	BDI	x																							x
	VAS-mood	x			x			x			x			x			x			x					x
Sleep	Scopa Sleep	x																							x
	VAS-sleep	x			x			x			x			x			x			x					x
ADL	NEAI	x												x											x
QoL	PDQ-8	x												x											x
Blood	BDNF/NfL, α-syn	x						x						x						x					x

*Planning of baseline (A1, A2, and A3), intervention (B and C), and measurements (crosses indicate time movements). Pre–post phase measurements will be performed before and after both baseline and both intervention phases*.

*UPDRS, MDS-Unified Parkinson's Disease Rating Scale; MoCa, Montreal Cognitive Assessment; PD-CFRS, PD Cognitive Functioning Rating Scale; Stroop, Stroop test; VAS, visual analog scale; BDI, Beck Depression Inventory; ADL, activities of daily living; Scopa Sleep, Sleep scale from Scopa; NEAI, Nottingham Extended ADL index; QoL, quality of Life; PDQ-8, Parkinson's Disease Questionnaire; BDNF, brain-derived neurotrophic factor; NfL, neurofilament light; α-syn, alpha synuclein*.

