### Statistical Analysis

Although the protocol specifies primary and secondary study outcomes, we will assess the results based on a combination of those parameters.

For example, the primary research parameter that we have specified is the MDS-UPDRS-III, which is measured before and after each phase. If, under the influence of the interventions, there are improvements within the participants that are greater than the measurement error of 3.25 points known from the literature (48), this is a clear indication that the intervention influences motor function. However, if there is less or no change in the MDS-UPDRS-III but in one or more other parameters, this is still informative with regard to the effects of the different interventions and the underlying mechanisms. If no change is visible in any parameter under the influence of the interventions in any participant (through visual analysis and/or statistical tests), then the conclusion should be that there is no effect.

Visual inspection is the method of choice for single-subject research designs (SSRDs) (24). We will inspect, analyze, and describe the changes across the baseline and intervention phases (phase mean level and data spread), and we will compare the trend (slope) of scores with the baseline mean levels and variability (standard deviations) on outcomes for each intervention strategy and each patient. Longitudinal regression analysis with “phase” (i.e., condition) as the independent variable will be used for further confirmation (α = 0.05).

We will not explicitly test for group differences between patients in Hoehn–Yahr stage 1–2 or for patients in Hoehn–Yahr stage 2.5–3, but we will get insights on the direction of effects and effect sizes in the intervention phases compared with the baseline phases, which we will report descriptively for both participants in both subgroups.

The association between biomarkers and symptom changes will be quantified by Pearson correlation coefficients and corrected for age, between changes in BDNF, α-synuclein, and Nfl and change scores on primary and secondary parameters.

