Reduced aerobic and anaerobic capacity are common in the elderly and especially in PD patients, though the rate of capacity reduction can be decreased by adopting a more active physical lifestyle (1). The experimental intervention in this study, HIIT, has already been used in sports science to improve both aerobic and anaerobic capacity (18); and preliminary studies are emerging in the field of PD. It is plausible that HIIT can be a time-efficient type of exercise that integrates both aerobic and anaerobic exercise, thereby enhancing the motivation of PD patients to comply with the intervention and in the long run promote a more active lifestyle. To our knowledge, we are the first to explore the within-subjects responses of blood biomarkers with weekly repeated measurements over multiple weeks (during baseline, washout, and intervention periods) for the two different exercise conditions. The design of the study allows for careful individual exploration of the response patterns of different exercise strategies on both symptoms and biomarkers. The advantage is that a small sample is enough to get important new knowledge, which will facilitate future well-powered clinical trials.

This study primarily explores whether HIIT is more effective at improving motor and cognitive performance than moderate CAE. If our hypothesis that HIIT is more effective than moderate CAE is correct, future HIIT studies in PD patients can add other treatment types, such as cognitive stimulation. For example, the Park-in-Shape study (60) investigated the feasibility of adding “exergaming” elements to improve adherence. Furthermore, a recent publication of a large observational study in PD patients in the Netherlands highlights the cost-effectiveness of specialized goal-based physical activity therapy by reducing both health-care cost and disease-related complications (61), which should be explored in future studies by combining HIIT with exercise goals beyond mere completion of the protocol.

To increase the societal relevance and impact of the current study protocol, two Parkinson patients who were consulted during the design process of this study expressed optimism about the procedures presented in this protocol. They also acknowledged the need for a better understanding of individual neural response patterns to different exercise intensities.

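### Stroop and Trail Making are repeated six times and read per patient by phase alone, so any practice gain mixes with training and creates an order difference whose direction depends on the reference

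*Protocol article*

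**What the plan says.** Outcome Measures lists the cognitive tests among the secondary outcomes: "Cognition will be evaluated with the MoCA (34), the Stroop test (35), and the Trail Making Test for executive function". In Table 1 the Stroop and TMT rows each carry six marks: one in A1, one in the first intervention, one in A2, one in the second intervention and two in A3.

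Two passages describe the boundary visits. Outcome Measures says that "pre–post intervention outcome measures will be administered before and after each study phase", and the footnote to Table 1 says that "Pre–post phase measurements will be performed before and after both baseline and both intervention phases". On this reading the mark at the first session of a phase closes the phase before it.

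On order, Study Design says: "The order of interventions B and C will be randomized for each participant (i.e., ABACA or ACABA, two of each, four participants total").

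On analysis, the Statistical Analysis section sets the reading at the level of the individual: "we will compare the trend (slope) of scores with the baseline mean levels and variability (standard deviations) on outcomes for each intervention strategy and each" (the last word refers to the patient). A longitudinal regression with phase as its independent variable serves as confirmation. On secondary outcomes the same section says that "if there is less or no change in the MDS-UPDRS-III but in one or more other parameters, this is still informative". The Discussion gives cognition weight: "This study primarily explores whether HIIT is more effective at improving motor and cognitive performance than moderate CAE".

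**The concern.** Stroop and TMT are timed tests, on which some improvement with repetition is plausible, probably most over the first attempts. The only score in the A1 columns is then the least practised one. The 10-m walk, TUG and one-leg stance have four values each in A1, so their early learning can be seen before training. For Stroop and TMT, A1 gives a single column value, which has no standard deviation and no slope, although the visual analysis relies on baseline level and variability.

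The analysis as described has no term for attempt number or time, and its main reading is patient by patient. A practice gain could therefore be reported as a cognitive response to exercise. Because the two blocks sit at different points on the learning curve, it could also be reported as a difference between HIIT and CAE in a single patient.

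**Working it through.** **Inputs from the documents.** Phase lengths are 4, 4, 8, 4 and 8 weeks, 28 in total (Study Design). The Stroop and TMT marks in Table 1 fall at these study weeks:

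| Attempt | Study week | Table 1 column | Role under the pre-post scheme |
|---|---|---|---|
| 1 | 1 | A1, week 1 | start of A1 |
| 2 | 5 | first intervention, week 1 | end of A1, before block 1 |
| 3 | 9 | A2, week 1 | after block 1 |
| 4 | 17 | second intervention, week 1 | before block 2 |
| 5 | 21 | A3, week 1 | after block 2 |
| 6 | 28 | A3, week 8 | end of A3 |

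**Assumption.** The documents give no practice effect, so the check assumes no training effect and a total practice gain G over six attempts. Scores are oriented so that higher is better. Three front-loaded curves for attempt n are scaled to 0 at attempt 1 and 1 at attempt 6:

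- Curve a, 1 − 1/n: 0, 0.60, 0.80, 0.90, 0.96, 1
- Curve b, 1 − exp(−0.5(n − 1)): 0, 0.43, 0.69, 0.85, 0.94, 1
- Curve c, 1 − exp(−(n − 1)): 0, 0.64, 0.87, 0.96, 0.99, 1

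**Reading 1: pre-post change.** Block 1 is attempt 3 minus attempt 2; block 2 is attempt 5 minus attempt 4.

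| Share of G | a | b | c |
|---|---|---|---|
| A1, untrained (1 to 2) | 60% | 43% | 64% |
| Block 1 (2 to 3) | 20% | 26% | 23% |
| Block 2 (4 to 5) | 6% | 10% | 3% |
| First minus second | +14% | +16% | +20% |

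As a sensitivity check, take a geometric curve on which 30% to 80% of the remaining gain is left after each attempt. As shares of its full (asymptotic) gain, block 1 gets 16–25%, block 2 gets 2–10%, and the first exercise leads by 6–19%.

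**Reading 2: Table 1 columns, A1 as reference.** The first exercise is attempt 2 minus attempt 1: 60%, 43%, 64%. The second is attempt 4 minus attempt 1: 90%, 85%, 96%. The second exercise is favoured.

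**Reading 3: phase-only regression with pooled A as reference.** Each block estimate is its score minus the mean of the four remaining scores. For curve a with column coding, pooled A = (0 + 0.80 + 0.96 + 1)/4 = 0.69. The first block is 0.60 − 0.69 = −0.09 and the second is 0.90 − 0.69 = +0.21.

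| Coding | Block | a | b | c |
|---|---|---|---|---|
| By Table 1 column (attempts 2 and 4) | first | −9% | −23% | −8% |
| | second | +21% | +19% | +24% |
| By post-block visit (attempts 3 and 5) | first | +17% | +12% | +22% |
| | second | +33% | +37% | +34% |

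The second exercise is favoured under either coding.

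**Reading 4: Table 1 columns, preceding A as reference.** The first exercise gets 60%, 43%, 64%. The second (attempt 4 minus attempt 3) gets 10%, 16%, 9%. The first exercise is favoured.

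**Average over orders.** If d is the first-block advantage and learning is alike, two patients contribute +d to HIIT minus CAE and two contribute −d: (2d − 2d)/4 = 0. This does not protect exercise against no exercise. The mean pre-post practice share per block is (20 + 6)/2 = 13%, (26 + 10)/2 = 18% and (23 + 3)/2 = 13% of G.

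**The case against.** A reader might infer that the plan favours whichever exercise comes first. The documents do not support that as a general statement. It holds for pre-post change and for comparison with the preceding A phase. It reverses when A1 or the pooled A phases are the reference, and the article does not fix the reference.

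A reader might also infer that the unpractised first attempt is the only pre-training value, so that the steepest learning is booked as training. Under the stated pre-post scheme the week 5 score is the pre-training value. The largest step (43–64% of G) then falls in untrained A1, where it can be seen as change without training.

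It is tempting to add that a straight-line week term would still leave 11–24% of G on the first block. That is true only if attempts 2 and 4 are coded as training values. The same fit assigns 11–17% to the second block, so little order difference remains, and the plan names no week term.

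Other points on the plan's side stand. The 2:2 order protects the four-patient average if learning is alike. These are secondary tests in an exploratory pilot of four, and cognition is also covered by the MoCA, the PD-CFRS and the concentration VAS. Calling a change informative is not a success rule. Alternate test forms and familiarisation are details an article may leave to the full protocol, so their absence here proves little.

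None of this removes the confounding within a patient, and the patient is the level at which the article says results will be read.

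**Conclusion.** The concern holds in a limited form. The schedule and the per-patient, phase-only analysis mix practice with training for Stroop and TMT. Under the assumed curves, each reading of the plan as written that was computed gives a spurious difference between the first and second exercise within a patient. On pre-post change it is 14–20% of G in favour of the first; with A1 or pooled A as reference it favours the second. The difference cancels only in the average over both orders, if learning is alike.

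The result rests on three assumptions that the documents neither state nor exclude: that practice gains occur, that they are front-loaded, and that they persist across the 8-week A2 phase. G has no absolute size here, so the check shows how the error behaves and not how large it is in test units.

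**What to change.** For Stroop and TMT only:

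1. Treat A1 week 1 as a familiarisation attempt that enters neither the baseline level nor the phase regression.
2. Compute block changes only as pre-post: week 5 to week 9 and week 17 to week 21. Dropping week 1 from the regression is not enough alone, because the choice of reference would still drive the order difference.
3. Report the week 1 to week 5 change, with no training between, beside the block changes as each participant's practice gain.
4. Draw any HIIT-versus-CAE conclusion on these tests from the average over both orders, not from single patients.

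This needs a note in the schedule and the analysis text, with no new visit or test. The cost is that one untrained reading leaves the baseline. Some practice also remains in block 1 (20–26% of G under the assumed curves), so a block change should be read as practice plus training.

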**Table d38e472:** 

**Schedule**																									
	**Phase**	**Baseline A1**												**Intervention B/C**											
	**Week**	**1**			**2**			**3**			**4**			**1**			**2**			**3**			**4**		
	**Session**	**s1**	**s2**	**s3**	**s1**	**s2**	**s3**	**s1**	**s2**	**s3**	**s1**	**s2**	**s3**	**s1**	**s2**	**s3**	**s1**	**s2**	**s3**	**s1**	**s2**	**s3**	**s1**	**s2**	**s3**
Tests	Cardiac Screening	x																							
	Demographics	x																							
	VO_2_ test												x												
Motor	UPDRSI-IV	x												x											
	TUG	x			x			x			x			x											
	10m walk	x			x			x			x			x			x			x			x		
	one-leg-stance	x			x			x			x			x			x			x			x		
Cognition	MoCa	x																							
	Stroop test	x												x											
	TMT	x												x											
	PD-CFRS	x												x											
	VAS-concentration	x			x			x			x			x	x	x	x	x	x	x	x	x	x	x	x
Mood	BDI	x												x											
	VAS-mood	x			x			x			x			x	x	x	x	x	x	x	x	x	x	x	x
Sleep	Scopa sleep	x												x											
	VAS-sleep	x			x			x			x			x	x	x	x	x	x	x	x	x	x	x	x
ADL	NEAI	x												x											
QoL	PDQ-8	x												x											
Blood	BDNF/NfL, α-syn	x			x			x			x			x			x			x			x

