**Table d38e1278:** 

	**Phase**	**Baseline A2**																								**Intervention C/B**											
	**Week**	**1**			**2**			**3**			**4**			**5**			**6**			**7**			**8**			**1**			**2**			**3**			**4**		
	**Session**	**s1**	**s2**	**s3**	**s1**	**s2**	**s3**	**s1**	**s2**	**s3**	**s1**	**s2**	**s3**	**s1**	**s2**	**s3**	**s1**	**s2**	**s3**	**s1**	**s2**	**s3**	**s1**	**s2**	**s3**	**s1**	**s2**	**s3**	**s1**	**s2**	**s3**	**s1**	**s2**	**s3**	**s1**	**s2**	**s3**
Tests	Cardiac Screening																																				
	Demographics																																				
	VO_2_ test																								x												
Motor	UPDRSI-IV	x																								x											
	TUG	x						x						x						x						x											
	10m walk	x						x						x						x						x			x			x			x		
	one-leg-stance	x						x						x						x						x			x			x			x		
Cognition	MoCa																									x											
	Stroop test	x																								x											
	TMT	x																								x											
	PD-CFRS	x																								x											
	VAS-concentration	x			x			x			x			x			x			x			x			x	x	x	x	x	x	x	x	x	x	x	x
Mood	BDI	x																								x											
	VAS-mood	x			x			x			x			x			x			x			x			x	x	x	x	x	x	x	x	x	x	x	x
Sleep	Scopa Sleep	x																								x											
	VAS-sleep	x			x			x			x			x			x			x			x			x	x	x	x	x	x	x	x	x	x	x	x
ADL	NEAI	x												x												x											
QoL	PDQ-8	x												x												x											
Blood	BDNF/NfL, α-syn	x						x						x						x						x			x			x			x

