### Training Protocol

Subjects will perform HIIT or moderate CAE on a stationary bicycle (Lode Corival, Lode Inc.) 3×/week for two periods of 4 weeks in a group of four subjects (Figure 1). The order of the intervention phases will be randomized. Training will take place on Mondays, Wednesdays, and Fridays, to allow for sufficient recovery periods between training sessions.

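### TUG is listed as a weekly motor outcome, but Table 1 schedules it only once in each training phase (week 1, session 1), and all three motor tests only every 2 weeks in A2 and A3

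*Protocol article*

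**What the plan says.** The Outcome Measures section opens its list of weekly motor outcomes with "Weekly outcomes are motor performance, namely, the 10-meter walk test (41), the Timed" Up-and-Go, and ends it with "test (TUG) (42), and the one-leg stance test (43". All three tests are given the same frequency, with no exception for any phase.

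Training runs "3×/week for two periods of 4 weeks in a group of four subjects", so each training phase has 12 sessions.

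Table 1 gives the visit schedule. Under "Intervention B/C" and again under "Intervention C/B", the 10 m walk and one-leg stance are marked at session 1 of weeks 1, 2, 3 and 4. TUG is marked at week 1 session 1 only. In A2 and A3 all three tests are marked at weeks 1, 3, 5 and 7, with one further mark at week 8 session 3 of A3. The table legend says: "Pre–post phase measurements will be performed before and after both baseline and both intervention phases".

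The Statistical Analysis section plans to describe "the changes across the baseline and intervention phases (phase mean level and data spread") and the slope of scores, for each intervention and each patient. A longitudinal regression with phase as the independent variable then serves as confirmation at α = 0.05.

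**The concern.** The stated frequency and the schedule cannot both be followed. A site working from Table 1 would stop TUG during training while continuing its two companion tests at the same visits. In A1, A2 and A3 the three tests share one schedule, so the gap affects TUG alone and falls only while training is under way. The article explains why blood draws are less frequent in A2 and A3, but gives no reason for dropping TUG.

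The first objective is the response pattern to HIIT compared with CAE, and the analysis reads that pattern from level, slope and spread within phases. With one TUG value at the start of each training phase, two of these three features do not exist, and the third reflects a participant who has had at most one session. If that value enters the regression under its Table 1 heading, TUG could show no phase effect whatever the training did. The article judges effects on a combination of parameters, so such a null could feed the overall conclusion.

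**Working it through.** **Inputs.** The frequency comes from Outcome Measures, the phase lengths from Study Design and Training Protocol, and the marks from the three blocks of Table 1. The row cells were split and each mark assigned to a phase, week and session.

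**Extraction check.** The TUG rows have 24, 36 and 24 cells. The phases need (4 + 4) × 3 = 24, (8 + 4) × 3 = 36 and 8 × 3 = 24. No cells are lost or shifted. The adjacent row, "10m walk x x x x x x x x", shows all eight marks for A1 and the first training phase, and the same TUG gap appears in two separate blocks of the table.

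**Counts per participant.**

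| Phase | Weekly, as the text says | TUG in Table 1 | 10 m walk in Table 1 |
|---|---|---|---|
| A1 (4 weeks) | 4 | 4 | 4 |
| First training (4 weeks) | 4 | 1 | 4 |
| A2 (8 weeks) | 8 | 4 | 4 |
| Second training (4 weeks) | 4 | 1 | 4 |
| A3 (8 weeks) | 8 | 5 | 5 |
| Total | 28 | 15 | 21 |

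One-leg stance follows the 10 m walk. The text's weekly frequency is reproduced for TUG only in A1. For the other two tests it is reproduced in A1 and both training phases, but not in A2 or A3.

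**Values after the first training day, within training.** TUG: 1 − 1 = 0 in each phase. 10 m walk and one-leg stance: 4 − 1 = 3 in each phase. Because both training phases have the same gap, it affects HIIT and CAE in either order.

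**Consequence for the analysis.**

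- A within-phase standard deviation or slope needs at least two values. With n = 1 neither exists for TUG under HIIT or CAE.
- Take a regression for one participant with phase as a categorical factor and no other terms. The HIIT effect is then (mean under HIIT) − (mean of the reference A values). With one HIIT value this is (HIIT week 1 session 1 value) − (A mean). The HIIT-versus-CAE contrast is likewise the difference between two start-of-phase values. Each single value is fitted exactly, so the residual variance comes only from A-phase values.
- If the four participants are pooled, each condition has 4 × 1 = 4 TUG values, all from the first training day.

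**What survives.** TUG is marked at week 1 session 1 of A2 and of A3, the first visit after each training phase. The change from week 1 session 1 of training to that visit gives one pre-post difference for HIIT and one for CAE in each participant.

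**If TUG followed the 10 m walk row.** 15 + 3 + 3 = 21 values, with 4 per training phase, 3 of them after training has begun.

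**The case against.** The strongest reply is that a single mark at the start of training is the normal pattern for pre-post measures in this plan. The MDS-UPDRS (whose part III is the primary outcome), Stroop, TMT, PD-CFRS, BDI and Scopa Sleep all have it, and the legend describes measurement before and after phases. Read that way, TUG is handled in training as the primary outcome is, and HIIT and CAE can still be compared through the two pre-post changes. This stands. A reader might infer from the gap that no TUG contrast carries training information, or that TUG cannot serve the first objective. The documents do not support either inference, because the A2 and A3 marks supply the post-training values.

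Three further limits also stand. The article does not say whether text or table governs; if the text does, TUG is measured weekly and nothing is lost. It does not say whether TUG at week 1 session 1 comes before or after that day's training, so the value is best called essentially untrained; at most one session could precede it. And TUG is not the primary outcome in this four-person exploratory pilot, where two other motor tests are scheduled weekly during training.

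The reply does not remove the contradiction. The article places TUG in the weekly list, separately from the pre-post measures, and schedules it with its companions everywhere except in training. Nor does it settle how the week 1 session 1 value enters the phase regression.

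**Conclusion.** The point holds as an inconsistency between text and table with a definite analytic consequence. Table 1 gives TUG 1 value per training phase against 4 for the 10 m walk and one-leg stance, and 0 against 3 after the first training day. It also marks all three tests less often than weekly in A2 and A3 (4 and 5 values, against 8 each if weekly). Provided Table 1 is the schedule followed, within-phase slope and spread cannot be estimated for TUG under either intervention. Provided also that the week 1 session 1 value is coded by its table heading, the phase regression represents HIIT and CAE by an essentially untrained value. The pre-post TUG change is unaffected, as are the primary outcome and the other two motor tests. This should be corrected, but it does not threaten the study as a whole.

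**What to change.** Reconcile the Outcome Measures text with Table 1. The preferred route has two parts:

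- Add TUG at session 1 of weeks 2, 3 and 4 in both training phases, where the 10 m walk and one-leg stance are already scheduled.
- State in the text that all three motor tests are done every 2 weeks in A2 and A3, with the closing measurement in A3.

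The cost is 3 + 3 = 6 short tests per participant, or 6 × 4 = 24 across the study, with no new visits.

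If TUG is meant to be limited in training, list it as a pre-post measure for those phases. Analyse its change from week 1 session 1 of training to week 1 session 1 of the following A phase, and do not code the week 1 session 1 value as a training-phase value in the regression. This costs only wording, but gives up the within-training pattern for TUG. The A2 and A3 frequency still needs correcting in the text.

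On either route, state whether testing at week 1 session 1 takes place before that day's training.
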